This study aims to address the knowledge gap by exploring the potential association between microbiota profiles, nutritional status and autism severity in children with ASD. Previous research has highlighted the potential role of gut microbiota imbalances, nutritional deficiencies, and their contribution to ASD progression [10,12–14,18,19,26–29]. However, there remains a lack of understanding of these relationships in Southeast Asia, particularly in Malaysia, where cultural and dietary practices may influence these factors differently from Western populations. This research is among the first comprehensive studies in Malaysia to simultaneously examine microbiota profile alongside nutritional status, particularly BMI and ASD severity. Existing studies have not fully integrated these components, often focusing solely on microbial diversity or gastrointestinal symptoms. The inclusion of nutritional status and a thorough analysis of dietary factors influenced by Malaysian culture are strengths of this study. The main strength of this research is its case-control study design, enabling the identification of specific microbiota and nutritional patterns associated with ASD severity as compared to TD healthy controls. By providing baseline data specific to the Malaysian context, this research aims to address the limited studies on the nutritional and microbiome profiles of children with ASD in Southeast Asia. With additional independent variables such as eating behaviour, behavioural profile, and sleep quality, the findings from this study could guide the development of targeted interventions, such as dietary modification or medical management, tailored to the unique needs of Malaysian children with ASD, ultimately enhancing their health and well-being.

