### Study Population and setting

Male children between 4–10 years old who comply with the protocol definition and inclusion criteria will be enrolled as participants. Cases are defined as male children diagnosed with ASD and receiving under follow-up care at the Paediatric Clinic at HTJ. Controls are defined as age-matched, TD healthy male children from daycare centres near IMU Healthcare and TABIKA KEMAS in Seremban. These locations were selected based on convenience sampling. Cases and controls are matched within using an age range of ±6 months.

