### Sample size

This study aims to compare the microbial community structure between the ASD and TD healthy groups and within the groups, generating plausible distances relevant to the study objectives. Beta diversity is used to estimate the sample size or statistical power for this study. The recommended sample size is 60 participants, determined based on calculations using data from a study conducted by Li et al. [31]. Due to the limited availability of similar studies, this prior research served as a reference to obtain appropriate variance estimates [31]. The total study sample size of 60 participants has been adjusted to account for a possible 30% dropout rate; thus, this study aims to recruit 80 participants (40 children with ASD and 40 TD healthy children). The primary outcomes are microbial beta diversity and nutritional status. Secondary microbiota comparisons will be adjusted for multiple testing using the Benjamini-Hochberg false discovery rate, and post-hoc power analyses will be conducted to assess adequacy for multivariate models.

The study included only male children to eliminate potential gender bias, as the male predominance in ASD has been well-documented in epidemiological studies and widely recognised in the field [32–34]. This approach also ensures greater homogeneity in the demographic and microbiome datasets, thereby enhancing the precision and reliability of the findings.

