### Data collection sheet

This sheet contains two sections as follows: (1) Information on participant and family demographics (child’s gender, age, gestational age, birth weight, parent’s age, ethnicity, occupation, education level, and household income); and (2) ASD medical history (age of first presentation, first presenting complaint, family history of ASD or other neurodevelopmental disorders (NDDs)) and other relevant medical conditions, if applicable.

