### Statistical analysis plan

Data analysis will be conducted using R software and its available packages. The differences in microbiota profiles, socio-demographic factors, emotional and eating behaviour, and nutritional status between children with ASD and TD children will be compared using the chi-square/Fisher’s exact test and ANOVA where appropriate. Student’s t-test will be applied to compare BMI and age between groups. Pre-filtering and inference of correlations will be performed using the Sparse Correlations for Compositional Data (SparCC) correlation metric [66], with a minimum R-value threshold of 0.35. SparCC will be used to correlate salivary and faecal bacterial markers detected in saliva and faecal samples from the same child. The associations between microbiota profiles, socio-demographic factors, emotional and eating behaviour, autism severity, sleep quality, gastrointestinal symptoms, and nutritional status among children with ASD will be modelled using mixed-effects logistic regression (MELR) model and random forest. Normality, linearity, homoscedasticity, and multi-collinearity will be assessed to ensure that the assumptions of regression models are met. Potential confounders, including age, and socioeconomic status will be adjusted for fixed effects. Model assumptions will be performed using DHARMa package in R to assess dispersion, zero-inflation and overall fit [67]. In case of heteroscedasticity or overdispersion, corrective strategies will include the use of an observation-level random effect, modelling dispersion or zero-inflation with glmmTMB [68], or applying bias-reduced logistic regression (Firth correction) [69] or bootstrap inference to mitigate small-sample bias [70]. Study results are expected in December 2026.

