## Discussion

This study primarily aims to determine oral and gut microbiota profiles among children with ASD and investigate potential associations between the oral and gut microbiota and various factors, including socio-demographic factors, nutritional status, and autism severity among ASD and TD healthy children. This study also measures additional outcomes to determine the associations between oral and gut microbiota and gastrointestinal symptoms, eating behaviour, behavioural profile, and sleeping quality. This study addresses a critical knowledge gap within the Malaysian context, where unique cultural norms and dietary patterns may shape gut microbiome composition in ways that diverge from Western cohorts. These findings have the potential to inform precision, culturally tailored interventions for Malaysian children with ASD, advancing both clinical practice and public health strategies.

Where such bacterial genomic markers show an association with ASD, these could have an impactful effect on enhancing our ability to stratify patients for personalised therapy. This research will contribute to the increasing significance of genomic medicine within the Malaysian healthcare sector. This study could widen opportunities for applying structural genomic liability in both clinical and pharmaceutical contexts. By contributing to the essential fundamental knowledge of the genetics of ASD, this research could lead to advancements in personalized medicine for ASD treatment in Malaysia, benefiting the healthcare industry and ultimately improving the quality of care provided to affected individuals. This may result in a reduced economic burden of treating diseases that are the direct or indirect consequences of ASD in Malaysia. In alignment with national health priorities, this study embraces the Government’s efforts in fighting obesity and other diet-related non-communicable diseases (NCDs) via the National Strategic Plan for Non-Communicable Disease (NSP-NCD) and the National Plan of Action for Nutrition of Malaysia III (NPANM III).

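### The ASD–TD microbiota contrast states no covariate, and ethnicity, which is recorded but not matched on, is not among the named confounders

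*Protocol article*

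**What the plan says.** All references are to the protocol article.

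- **Group comparison** (Statistical analysis plan). Differences between ASD and TD children in microbiota profile, socio-demographic factors, behaviour and nutritional status "will be compared using the chi-square/Fisher’s exact test and ANOVA where appropriate". No covariate is stated for this comparison.
- **Regression** (same section). Associations among microbiota, socio-demographic factors, nutritional status and the other measures are modelled in the ASD group only: "nutritional status among children with ASD will be modelled using mixed-effects logistic regression (MELR) model and random forest". The adjustment sentence follows that model: "Potential confounders, including age, and socioeconomic status will be adjusted for fixed effects".
- **Data** (Data collection sheet). The demographics section records "ethnicity, occupation, education level, and household income".
- **Design** (Study Population and setting; Sample size). "Cases and controls are matched within using an age range of ±6 months", and the study is restricted by sex: "The study included only male children to eliminate potential gender bias". There is no matching or restriction on ethnicity. Cases come from a hospital paediatric clinic; controls come from daycare centres and TABIKA KEMAS. The locations are a convenience choice.
- **Rationale.** The Background treats diet as a main determinant of gut microbial diversity. The Review of previous literature describes Malaysia as a setting "where cultural and dietary practices may influence these factors differently from Western populations", and the Discussion says that "unique cultural norms and dietary patterns may shape gut microbiome composition in ways that diverge from Western cohorts".

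**The concern.** Microbial beta diversity is a primary outcome (Sample size section), so the ASD–TD contrast is the central result. As written, it is controlled only by age matching and the restriction to boys. The two groups are drawn through different routes, and nothing in the design makes their ethnic composition alike. If ethnicity is related to diet and so to the microbiota, a difference in ethnic mix would pass into the unadjusted contrast and could be reported as an ASD-related difference. Comparing socio-demographic factors between groups would show such an imbalance but would not remove it.

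The same question arises, less sharply, within the ASD group. Ethnicity could influence both diet or BMI and microbiota, so a nutrition–microbiota association could partly reflect it. Matching to controls cannot help there; only adjustment can.

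**Working it through.** The plan gives no figure on this point, so there is none to reproduce. The documents give neither ethnic shares nor an ethnic effect on the microbiota. The only design number used is the recruitment target of 40 per group; everything else below is assumed.

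**Step 1: the passages side by side**

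| Question | Answer in the protocol |
|---|---|
| Is ethnicity recorded? | Yes (Data collection sheet) |
| Is it a matching or restriction factor? | No: age within 6 months, boys only |
| Covariates in the ASD–TD contrast | None stated |
| Named confounders for the within-ASD regression | Age and socioeconomic status, as examples |
| Do cases and controls share a source? | No |

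**Step 2: bias of an unadjusted two-group comparison.** Take a continuous outcome with within-stratum SD 1, a two-level ethnic stratum with effect g (in SD), stratum shares p1 in ASD and p0 in TD, and no true ASD effect.

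Expected apparent ASD effect = g × (p1 − p0).

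Results for g = 0.5 and g = 0.8, from 4000 simulated data sets per scenario, two-sided 0.05, 40 per group:

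| Shares (ASD vs TD) | Gap | Size of apparent effect (SD) | False positives, unadjusted | With ethnicity as covariate |
|---|---|---|---|---|
| 60% vs 60% | 0 | 0 | 5.0%, 5.1% | 5.0%, 5.1% |
| 60% vs 75% | 15 points | 0.075, 0.12 | 5.8%, 8.3% | 5.0%, 5.3% |
| 60% vs 90% | 30 points | 0.15, 0.24 | 9.3%, 17.7% | 4.9%, 5.0% |
| 50% vs 90% | 40 points | 0.20, 0.32 | 13.5%, 27.1% | 5.0%, 4.8% |

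Hand check for 60% vs 90%, g = 0.8:
- Average variance = 1 + 0.64 × (0.24 + 0.09)/2 = 1.106.
- Standard error = √(1.106 × 2/40) = 0.235.
- 0.24/0.235 = 1.02.
- Rejection probability ≈ Φ(1.02 − 1.96) + Φ(−1.02 − 1.96) = 0.174 + 0.001 = 0.175, against 0.177 simulated.

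With 30 per group the unadjusted rates are 5.3–6.3% (15 points), 9.2–14.0% (30 points) and 11.3–21.2% (40 points).

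**Step 3: a whole-community comparison.** A permutation test on community distances (PERMANOVA, which the protocol does not name) was simulated with 100 logistic-normal taxa. Ethnicity shifted 20 of them and explained about 4% or 9% of community variance. Each scenario used 200 data sets of 99 permutations.

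| Gap | 40 per group, unadjusted | 28 per group, unadjusted |
|---|---|---|
| 30 points (75% vs 45%) | 15.5%, 26% | 5%, 20.5% |
| 40 points (85% vs 45%) | 18%, 55% | 11%, 37% |

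The 28 is what remains per group if the planned 30% dropout occurs: 80 × 0.70 = 56. With ethnicity as a covariate and permutation within ethnic strata, the rate at 40 per group was 4.5–6.5%. Monte Carlo error is appreciable: √(0.155 × 0.845/200) ≈ 2.6 points and √(0.55 × 0.45/200) ≈ 3.5 points.

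**Step 4: chance imbalance.** If both sources had the same 60% share, a gap of at least 15 points would still arise with probability about 0.21 at 40 per group, and one of at least 20 points with probability about 0.09. Averaged over repetitions this does not raise the 5% error rate (first row of the Step 2 table), but in the realised sample the contrast would still carry the imbalance.

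**Step 5: within ASD.** No calculation was made. Socio-demographic factors are among the modelled variables, so ethnicity may enter there. The text does not commit to it as an adjustment for the nutrition–microbiota association.

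**The case against.** The strongest case against is that the article condenses a fuller plan. The word *including* makes age and socioeconomic status examples, and no sentence excludes ethnicity. A reader might infer that the protocol rules out adjusting for ethnicity; it does not, and the exact statement is that ethnicity is not named. This stands for the within-ASD models, where ethnicity may also enter among the socio-demographic factors. It does less for the ASD–TD contrast, whose stated tests carry no covariate at all.

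A reader might also infer that the protocol itself says ethnic groups in Malaysia differ in microbiota. It does not. Both cultural statements contrast Malaysia with Western populations and use *may*; the step to groups within Malaysia is an inference, though a reasonable one.

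Nor do the documents show that an imbalance exists. Controls are recruited in Seremban, where the hospital also lies, and no ethnic shares are reported. The 30- and 40-point gaps are severe assumptions. At 15 points the inflation is small, at equal shares there is none, and the mildest 28-per-group scenario shows none either. The upper rate of 55% depends on one model and should not be taken as a forecast.

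Finally, diet is measured directly by 3-day recall. That does not replace adjustment for ethnicity. Diet is not named as a covariate, and because the protocol describes restricted eating as a feature of ASD, diet may lie on the path from ASD to microbiota. Adjusting for it would answer a different question.

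**Conclusion.** The point holds in a limited form. Followed as written, the main ASD–TD microbiota contrast has no protection against a difference in ethnic mix, although the variable is already collected and the two groups come from different sources. The size of any bias is unknown. At 40 per group it ranges from nothing (equal shares, about 5% false positives), through 6–8% (15-point gap), to about 9–26% (30-point gap, both models together). Higher rates arose only with a 40-point gap. Adjustment returns the rate to about 5–7%.

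These figures assume a two-level stratum with an effect of 0.5 to 0.8 SD, or 4–9% of community variance, and no true ASD effect. For the within-ASD models the conclusion is weaker: ethnicity is not named as an adjustment but may already be included.

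**What to change.** Before analysis, amend the Statistical analysis plan in two places.

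1. **ASD–TD microbiota contrast.** Name ethnicity, with small groups merged by a rule fixed in advance, as a covariate alongside age and socioeconomic status. Replace the unadjusted ANOVA by a covariate-adjusted model or, for a permutation test, permute within ethnic strata.
2. **Within-ASD nutrition–microbiota models.** Add ethnicity to the named confounders where the number of events allows. With at most 40 ASD children in a logistic model this will not always be possible, so state in advance which models will carry it.

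No change to control selection is proposed: data collection began in August 2024, and altering the choice of controls partway would be more than a change of wording.

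The cost is 1–3 degrees of freedom per model and slightly wider intervals. No new data are needed. Fixing the covariate now also avoids adding it only after an imbalance has been seen.

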### Ethics approval and dissemination

This study has obtained ethics approval from the International Medical University Joint-Committee (IMU-JC) on Research & Ethics (Project ID: IMU R 299–2023) and the Medical Research & Ethics Committee (MREC) Ministry of Health (MOH) Malaysia (MREC ID: 23–03545-Q1W). Site approval has also been obtained from the Clinical Research Centre in HTJ, Seremban. Participation is voluntary, with written consent provided for the Parent Information Sheet (PIS), Informed Consent Form (ICF), ICF for future studies, Children’s Assent Form, and Children’s Assent for Biological Sample Collection. There are no severe side effects known to be caused by the assessment. This is an observational study with no interventions; parents are required to complete the questionnaires and faecal sample collection whereas investigators collected the child’s weight, height, and saliva sample, resulting in minimal risk for subjects. Subjects and their samples are linked to the study identification number, with no personal identifiers exposed. All personal and medical information obtained from the subject is kept in a password-protected database under the supervision of IMU University, Kuala Lumpur, Malaysia. Data and specimens are overseen by the MREC, MOH, and IMU-JC. Study results will be disseminated through peer-reviewed publications and conference presentations.

### Patient and public involvement

ASD patients are having their follow-up consultation with medical practitioners, eligible patients are invited to provide consent to take part in the study. ASD children’s parents are briefed on methods of self-collection stool samples. All other study outcomes are assessed by researcher and parents are not involved in the design, conduct, choice of outcome measures or the result dissemination of the study.

## Discussion

This study primarily aims to determine oral and gut microbiota profiles among children with ASD and investigate potential associations between the oral and gut microbiota and various factors, including socio-demographic factors, nutritional status, and autism severity among ASD and TD healthy children. This study also measures additional outcomes to determine the associations between oral and gut microbiota and gastrointestinal symptoms, eating behaviour, behavioural profile, and sleeping quality. This study addresses a critical knowledge gap within the Malaysian context, where unique cultural norms and dietary patterns may shape gut microbiome composition in ways that diverge from Western cohorts. These findings have the potential to inform precision, culturally tailored interventions for Malaysian children with ASD, advancing both clinical practice and public health strategies.

Where such bacterial genomic markers show an association with ASD, these could have an impactful effect on enhancing our ability to stratify patients for personalised therapy. This research will contribute to the increasing significance of genomic medicine within the Malaysian healthcare sector. This study could widen opportunities for applying structural genomic liability in both clinical and pharmaceutical contexts. By contributing to the essential fundamental knowledge of the genetics of ASD, this research could lead to advancements in personalized medicine for ASD treatment in Malaysia, benefiting the healthcare industry and ultimately improving the quality of care provided to affected individuals. This may result in a reduced economic burden of treating diseases that are the direct or indirect consequences of ASD in Malaysia. In alignment with national health priorities, this study embraces the Government’s efforts in fighting obesity and other diet-related non-communicable diseases (NCDs) via the National Strategic Plan for Non-Communicable Disease (NSP-NCD) and the National Plan of Action for Nutrition of Malaysia III (NPANM III).

The exclusion of children with ASD on medications is justified, as individuals with neuropsychiatric conditions often receive medications that can alter gut microbial communities [71]. Similar studies have also adopted this approach to minimize potential confounding effects on microbiota profiles in ASD [72]. This exclusion is therefore crucial to ensure an accurate assessment of the baseline microbial profile and better understand its relationship with ASD. Future intervention studies involving medicated children may instead aim to explore microbiota changes in response to specific pharmacological treatments.

The limitations of this study include its observational case-control design, reliance on parent-reported measures, and convenience sampling approach. Although observational in design, this study offers a critical foundation for future interventional research. The identified patterns may inform culturally tailored strategies such as probiotic supplementation or dietary modification to optimise child health in Malaysia. These applications, however, lie beyond the scope of the current protocol and require rigorous evaluation in longitudinal or randomised trials. Future longitudinal studies examining changes in the microbiome over time and in response to interventions could provide even more novel insights. Additionally, investigating serum indicators may help to optimise the evaluation of nutritional status.
